#### Primary outcome analysis

Between-group differences in the primary outcome measure, self-selected gait speed on discharge, will be assessed using a one-way ANCOVA model that will include self-selected gait speed at baseline as a covariate.

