**Methods/Design:**

A single blind, parallel-group, multisite randomized controlled trial with blinded assessment of outcome and intention-to-treat analysis. The cost effectiveness of the intervention will also be examined. Older people (age >60 years) undergoing inpatient rehabilitation to improve mobility will be recruited from geriatric rehabilitation units at two Australian hospitals. A computer-generated blocked stratified randomization sequence will be used to assign 198 participants in a 1:1 ratio to either an ‘enhanced physical activity’ (intervention) group or a ‘usual care plus’ (control) group for the duration of their inpatient stay. Participants will receive usual care and either spend time each week performing additional physical activities such as standing or walking (intervention group) or performing an equal amount of social activities that have minimal impact on mobility such as card and board games (control group). Self-selected gait speed will be measured using a 6-meter walk test at discharge (primary outcome) and 6 months follow-up (secondary outcome). The study is powered to detect a 0.1 m/sec increase in self-selected gait speed in the intervention group at discharge. Additional measures of mobility (Timed Up and Go, De Morton Mobility Index), function (Functional Independence Measure) and quality of life will be obtained as secondary outcomes at discharge and tertiary outcomes at 6 months follow-up. The trial commenced recruitment on 28 January 2014.

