### Randomization

As study site and mobility on admission are potential confounders, randomization will be blocked and stratified by site and mobility level. At baseline, the mobility of participants will be classified as either non-ambulant (Level 1 or 2 as detailed in Table 1) or ambulant (Level 3 or 4 as detailed in Table 1)*.* This classification will be used for stratification by mobility level. Once consent has been obtained and baseline data collected, participants will be individually randomized to an intervention group (enhanced physical activity) or a control group (usual care plus) according to a computer generated randomization procedure performed by a third party. Group assignment will only be available to intervention staff and the project manager, and will be accessed online via a password protected site.

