### Outcome measures

#### Primary outcome

The primary outcome measure is mobility on discharge from hospital as assessed using gait speed. This will be measured using the 6-meter walk test [27] at self-selected speed by a trained assessor blinded to group allocation. Participants will be instructed to walk at self-selected speed along a 10-meter walkway, and a stopwatch will be used to measure speed over the middle 6 meters. Participants will be allowed to use a gait-aid if required, and this will be recorded. Up to three trials will be performed, and the best performance recorded. Participants unable to complete the test will be given a score of 0 m/sec. Gait speed was chosen as a primary outcome measure as it is associated with the need for long-term care [8], functional dependence, mortality [9] and falls [10]. Gait speed can also predict activity levels at home and in the community [28,29] and increases in gait speed are associated with improvements in overall health status [30]. Furthermore, gait speed has good retest reliability [27,31] and is responsive to changes in walking ability [32-34].

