#### Baseline

The baseline assessment will be completed within 48 hours of admission. In addition to primary and secondary outcome measures collected at baseline, additional demographic and clinical data will be obtained. These data will include the participant’s age, sex, height and weight, acute LOS, mental state (measured by the Mini Mental State Examination [42]), frailty (measured using the modified Fried Frailty Index) [43,44], co-morbidities (age adjusted Charlson Comorbidity Score [45]), depression (Geriatric Depression Scale [46]), medications, self (or carer) reported falls in the last 12 months and social situation.

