### Sample size estimation

The sample size for this study was calculated based on pilot data, which showed that the median gait speed of people discharged from aged care rehabilitation was 0.46 m/sec (range 0.1 to 1.2 m/sec) [6], which allowed a mean gait speed (0.46 m/sec) and variance (0.18 m/sec) to be estimated [50]. Sample size estimation was based on the intervention group achieving an increase in gait speed of at least 0.1 m/sec compared with the control group, the recommended minimal clinically important difference for gait speed in older adults [30,51]. With a two-tailed significance threshold alpha of 0.05 and power to yield a statistically significant result set at 90%, a sample size of 69 participants in each group is required. To account for an estimated 25% dropout rate and 14% of participants being unable to complete the walk test on discharge, as observed in pilot data [6,25], an estimated 198 participants will be required in total [52]. A recruitment rate of 34% was achieved in the pilot study. Based on average hospital admissions to the selected sites in this trial, and using a conservative recruitment rate of 20%, it is anticipated that the recruitment will be completed over 13 months.

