#### Secondary outcomes analyses

Between-group differences in gait speed 6 months postdischarge will be assessed using a one-way ANCOVA model that will include self-selected gait speed at baseline as a covariate;

Between-group differences in TUG on discharge will be assessed using a Cox regression model that will include self-selected gait speed at baseline as a covariate;

Between-group differences in DEMMI score on discharge will be assessed using a one-way ANCOVA model that will include DEMMI score at baseline as a covariate;

Between-group differences in FIM score on discharge will be assessed using a median regression model that will include the FIM score at baseline as a covariate;

Between-group differences in EQ5D score on discharge will be assessed using a median regression model that will include the EQ5D score at baseline as a covariate;

Between-group differences in subacute LOS will be assessed using a median regression model that will include the FIM score at baseline as a covariate.

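### The primary ANCOVA leaves out site and mobility level, the two stratification factors; adding them is a free improvement that keeps the test from being conservative if either predicts discharge gait speed beyond baseline gait speed

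*Protocol article*

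**What the plan says.** The Randomization section of the protocol article gives the reason for stratifying: "As study site and mobility on admission are potential confounders, randomization will be blocked and stratified by site and mobility level". Mobility level enters as a two-level factor: "the mobility of participants will be classified as either non-ambulant (Level 1 or 2 as detailed in Table 1) or ambulant (Level 3 or 4" in the same table). The abstract says that participants "will be recruited from geriatric rehabilitation units at two Australian hospitals", so there are four strata.

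The Primary outcome analysis section then fixes the confirmatory model: discharge gait speed "will be assessed using a one-way ANCOVA model that will include self-selected gait speed at baseline as a covariate". The general Statistical analysis section adds no stratification term. Each model under Secondary outcomes analyses likewise has one baseline covariate. For example: "Between-group differences in DEMMI score on discharge will be assessed using a one-way ANCOVA model that will include DEMMI score at baseline as a covariate".

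One scoring rule bears on the point. In the Primary outcome section, "Participants unable to complete the test will be given a score of 0 m/sec". The Baseline section confirms that the primary outcome measure is also taken at admission, so participants who cannot walk then enter the model with a covariate value of zero.

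**The concern.** Blocking within strata balances the arms on site and mobility level. The true sampling variance of the treatment difference is therefore already reduced by whatever those factors explain. A model that omits them does not know this. It leaves their contribution in the residual and reports a standard error larger than the true one. The consequences are wider intervals, a type I error below the nominal 5% and some lost power.

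Baseline gait speed is in the model, so only the part it fails to carry matters. It carries no direct information on site. It carries most of the mobility stratum, but a single straight line has to fit both a cluster at zero and the spread of walkers, so some mobility effect can remain. At stake is a modest amount of precision in the confirmatory test of a trial that took the trouble to stratify.

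**Working it through.** **Step 1. The plan's own figure.** Inputs from Sample size estimation: difference 0.10 m/sec, two-sided alpha 0.05, power 90%, 1:1 allocation, and 0.18 m/sec, which the text calls a variance but which works as a standard deviation (SD).

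n per group = 2 × (1.960 + 1.282)² × 0.18² / 0.10² = 68.1, rounded up to 69. This matches the protocol. With 69 per group the standard error (SE) is 0.18 × √(2/69) = 0.0306 and power is 90.4%. The calculation uses the raw SD and takes no credit for a covariate or for strata.

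**Step 2. Analytic effect of omitting the strata.** Let R² be the share of residual variance that site and mobility level explain beyond baseline gait speed. The documents give no R², so the values below are assumptions. The true SE is 0.0306 × √(1 − R²), and the reported SE exceeds it by a factor 1/√(1 − R²).

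| Assumed R² | SE too wide by | Type I error, strata omitted | Power, omitted → included (n = 69 per group) |
|---|---|---|---|
| 0 | 0% | 0.050 | 90.4% → 90.4% |
| 0.02 | 1.0% | 0.048 | 90.6% → 90.9% |
| 0.05 | 2.6% | 0.044 | 90.9% → 91.7% |
| 0.10 | 5.4% | 0.039 | 91.5% → 93.1% |
| 0.20 | 11.8% | 0.028 | 92.7% → 95.4% |

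**Step 3. Simulation.** From the documents: 198 participants, two sites, 1:1 allocation, stratification by site and mobility, and a score of 0 for those unable to walk. Assumed: equal-sized sites, 20% or 40% non-ambulant (all scoring 0 at baseline), walkers' baseline speed normal with mean 0.45 and SD 0.18 m/sec (floored at 0.05), slope 0.6 on baseline speed, residual SD 0.15, and blocks of 4. There were 3,000 replicates under the null. Ranges cover the two non-ambulant percentages.

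| Assumed effect beyond baseline gait speed (m/sec) | Mean SE, planned model | Mean SE, strata added | SE too wide by | Type I error, planned | Type I error, strata added |
|---|---|---|---|---|---|
| None | 0.0213 | 0.0213–0.0214 | 0% | 0.047–0.052 | 0.048–0.052 |
| Site 0.05 | 0.0216 | 0.0213–0.0214 | about 1% | 0.047–0.053 | 0.052–0.054 |
| Mobility 0.10 | 0.0216–0.0217 | 0.0213–0.0214 | 1–1.5% | 0.048–0.051 | 0.049–0.050 |
| Site 0.05 and mobility 0.10 | 0.0219–0.0220 | 0.0213–0.0214 | about 3% | 0.042–0.050 | 0.043–0.056 |
| Site 0.10 | 0.0224–0.0225 | 0.0213–0.0214 | about 5% | 0.037–0.038 | 0.049–0.052 |
| Site 0.10 and mobility 0.20 | 0.0236–0.0237 | 0.0213–0.0214 | about 11% | 0.031–0.035 | 0.042–0.052 |

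The Monte Carlo error of a 5% rejection rate is √(0.05 × 0.95 / 3000) = 0.004. Only the last two rows show type I error clearly below nominal.

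Hand check of the site 0.10 row: two equal sites differing by 0.10 contribute variance 0.05² = 0.0025 against a residual of 0.15² = 0.0225, and √(1 + 0.0025/0.0225) = 1.054. If 0.18 is instead taken as the total SD including site, the factor is 1/√(1 − 0.0025/0.0324) = 1.041.

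**Step 4. Where the loss sits.** In the site 0.10 row the actual spread of the planned model's estimates was 0.0211–0.0212, against 0.0212 with strata added. The estimator already has the precision, and only its reported SE (0.0224–0.0225) is too wide.

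**Step 5. How much baseline gait speed already recovers.** With no site effect and no extra mobility effect, a model with no covariate has SE 0.0296–0.0308. The planned model has 0.0213, and adding the strata gains nothing further.

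**Step 6. Power.** A 0.07 m/sec effect is used because 0.07/0.0213 = 3.29 gives about 90% power in this setting (1,500 replicates). With a site difference of 0.10, power was 89% for the planned model and 90–91% with strata. Adding a 0.20 mobility effect made it 84–85% against 90–91%.

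**The case against.** The strongest reply is that the planned covariate already does most of the work. The mobility stratum separates those who walk from those who do not, and the covariate is walking speed with zero for those unable to complete the test, so the two largely coincide. Step 5 bears this out. What remains is chiefly site, and the two hospitals lie in one metropolitan area and share eligibility criteria. A gap of 0.10 m/sec between them would equal the treatment difference the trial is designed to detect. All of this stands, and it is why the size must be stated conditionally.

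A reader might go further than the documents allow in four ways:

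- **That the standard error is certainly too wide and the gain from stratifying is lost outright.** The documents report no site effect and no residual mobility effect, and with neither the cost is nil.
- **That the estimate is confounded, because the protocol calls these factors potential confounders.** Stratified blocking balances them whichever model is fitted. The error is conservative: it causes no bias and does not inflate type I error.
- **That the stated power depends on this.** The 69 per group uses the raw SD and reproduces without any stratum adjustment. Whether the inflation to 198 is adequate is a separate question.
- **That the median regression, Cox and multiple-imputation models need the same change.** The calculations cover only a linear model for gait speed. Covariates in a Cox model also change the conditional hazard ratio being estimated, and the imputation model is ordinary SAP content.

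A SAP that is not shown might include the strata. The protocol, however, does not leave the primary model open. It names one without them, so the two documents would then need to be aligned.

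**Conclusion.** The point holds as a free improvement, not as a flaw that endangers the result. The design stratifies on two factors and the named primary model contains neither. If they predict discharge gait speed beyond baseline gait speed, the reported SE is too wide and the test is conservative.

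Under modest assumed effects taken singly, the excess is within about 1.5%, and it is about 3% when the two modest effects are combined. It takes a site difference of 0.10 m/sec to reach about 5%, and that difference plus a 0.20 m/sec residual mobility effect to reach about 11%. These figures rest on the assumed effects and the simulation settings listed above. The direction of the error and the absence of bias follow from the stratified design and do not depend on those settings.

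**What to change.** Prespecify the primary ANCOVA as treatment group + baseline gait speed + site + mobility stratum (non-ambulant/ambulant, as used at randomization). Add the same two terms to the secondary ANCOVAs for gait speed at 6 months and DEMMI at discharge. The argument carries over to those linear models, although no simulation was run for them. Make the change before unblinding, so that adjusted and unadjusted results are not chosen between afterwards.

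The cost is one line of wording and two degrees of freedom, with no new data, since both factors are recorded in order to randomize. If neither factor predicts the outcome, the simulated SE moves from 0.0213 to at most 0.0214, so essentially nothing is lost.

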#### Secondary outcomes analyses

Between-group differences in gait speed 6 months postdischarge will be assessed using a one-way ANCOVA model that will include self-selected gait speed at baseline as a covariate;

Between-group differences in TUG on discharge will be assessed using a Cox regression model that will include self-selected gait speed at baseline as a covariate;

Between-group differences in DEMMI score on discharge will be assessed using a one-way ANCOVA model that will include DEMMI score at baseline as a covariate;

Between-group differences in FIM score on discharge will be assessed using a median regression model that will include the FIM score at baseline as a covariate;

Between-group differences in EQ5D score on discharge will be assessed using a median regression model that will include the EQ5D score at baseline as a covariate;

Between-group differences in subacute LOS will be assessed using a median regression model that will include the FIM score at baseline as a covariate.

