#### Secondary outcomes

Secondary outcome measures include mobility on discharge from hospital as assessed using the Timed Up and Go (TUG) [31,35] and the De Morton Mobility Index (DEMMI) [36-38]. Gait speed will also be measured 6 months postdischarge as a secondary outcome measure. Additional secondary outcomes include function, as measured using the Functional Independence Measure (FIM^TM^) [39], health-related quality of life, as measured by the EuroQol health questionnaire (EQ5D) and the EuroQol Visual Analog Scale (EQ-VAS) [40] and subacute length of stay (LOS). These tests will be administered in accordance with previously published protocols. If a participant is unable to complete the EQ5D or EQ-VAS due to cognitive impairment, a proxy will complete it on their behalf.

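### Discharge TUG is adjusted for baseline gait speed but not for its own recorded baseline, which probably leaves some precision unused in one supplementary secondary analysis

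*Protocol article*

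**What the plan says.** The protocol article lists TUG at discharge among the secondary mobility outcomes. Its model is fixed under Secondary outcomes analyses: "Between-group differences in TUG on discharge will be assessed using a Cox regression model that will include self-selected gait speed at baseline".

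Under Assessments, the Baseline subsection confirms that the secondary measures are taken at that visit: "In addition to primary and secondary outcome measures collected at baseline, additional demographic and clinical data will be obtained". A baseline TUG is therefore recorded for those who can do it.

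The neighbouring models follow another pattern. The primary outcome "will be assessed using a one-way ANCOVA model that will include self-selected gait speed at baseline as a covariate". DEMMI has a "one-way ANCOVA model that will include DEMMI score at baseline as a covariate". For FIM, "Between-group differences in FIM score on discharge will be assessed using a median regression model that will include the FIM score at baseline". EQ5D likewise uses its own baseline.

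**The concern.** The usual covariate for an outcome measured before and after treatment is its own baseline value. The plan applies that to four outcomes and departs from it for TUG without comment. TUG includes rising from a chair and turning, so its baseline may carry information on discharge TUG that straight-line walking speed does not. If it does, the TUG comparison is less precise than data already collected would allow.

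This is a choice the article states, not a detail left to an analysis plan that is not shown. The article also says that 6-month outcomes, which include TUG, will be adjusted for the relevant baseline measures. If that means baseline TUG, the same test would be adjusted differently at the two time points.

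**Working it through.** **1. Covariates side by side** (Primary outcome analysis; Secondary outcomes analyses)

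| Outcome | Baseline value recorded? | Named covariate |
|---|---|---|
| Gait speed, discharge and 6 months | yes | own baseline |
| DEMMI, discharge | yes | own baseline |
| FIM, discharge | yes | own baseline |
| EQ5D, discharge | yes | own baseline |
| TUG, discharge | yes | gait speed |
| Subacute LOS | none exists | FIM |

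TUG is the only repeated outcome in the table without its own baseline.

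**2. The plan's own figures.** For gait speed, with a difference of 0.1, an SD of 0.18, two-sided alpha 0.05 and 90% power: n = 2 x (1.960 + 1.282)^2 x 0.18^2 / 0.1^2 = 68.1, so 69 per group, as stated (power at 69 is 0.904). The total of 198 is reproduced by 69 x 1.25 x 1.14 = 98.3, rounded up to 99 and doubled. Neither figure involves the TUG covariate. The article gives no power, SD or correlation for TUG, so everything below rests on assumed values.

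**3. Replacing or adding: linear approximation, everyone able to do both tests.** Let r_T and r_G be the correlations of discharge TUG with baseline TUG and baseline gait speed, all scored so that higher is better, and let the two baselines correlate at 0.8.

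- Replacing gait speed by TUG: variance ratio = (1 - r_G^2) / (1 - r_T^2).
- Adding TUG to gait speed: variance ratio = (1 - r_G^2) / (1 - R^2), with R^2 = (r_T^2 + r_G^2 - 2 x 0.8 x r_T x r_G) / (1 - 0.8^2).

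| r_T | r_G | Replace | R^2, both | Add |
|---|---|---|---|---|
| 0.7 | 0.7 | 0.51/0.51 = 1.00 | 0.196/0.36 = 0.544 | 0.51/0.456 = 1.12 |
| 0.7 | 0.6 | 0.64/0.51 = 1.26 | 0.178/0.36 = 0.494 | 0.64/0.506 = 1.27 |
| 0.7 | 0.5 | 0.75/0.51 = 1.47 | 0.180/0.36 = 0.500 | 0.75/0.500 = 1.50 |
| 0.6 | 0.7 | 0.51/0.64 = 0.80 | 0.178/0.36 = 0.494 | 0.51/0.506 = 1.01 |

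A ratio above 1 favours the model with TUG. Replacement can go either way. Adding cannot lower the variance explained, apart from the cost in degrees of freedom, but the gain can be almost nil.

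**4. Cox simulation with people unable to do the test.** Settings: 148 analysed (198 x 0.75 = 148.5); 14% unable at discharge, censored (the article's figure for the walk test, borrowed for TUG; the censoring is an assumption); treatment effect 0.4 SD; correlation 0.8 between the baselines; 10, 25 or 40% unable at baseline; 1,500 runs per scenario. Power at 10/25/40% unable:

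| r_T, r_G | Gait speed (as planned) | Baseline TUG, completers only | Baseline TUG + unable indicator |
|---|---|---|---|
| 0.7, 0.7 | 0.86/0.85/0.82 | 0.83/0.75/0.67 | 0.86/0.85/0.84 |
| 0.7, 0.6 | 0.79/0.77/0.76 | 0.83/0.76/0.67 | 0.86/0.85/0.84 |
| 0.7, 0.5 | 0.71/0.73/0.70 | 0.83/0.77/0.67 | 0.86/0.87/0.83 |
| 0.6, 0.6 | 0.79/0.78/0.76 | 0.76/0.70/0.58 | 0.79/0.80/0.79 |

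Without adjustment, power was about 0.58 to 0.62 throughout, so the planned covariate already recovers much of what is available. Compared with gait speed, the indicator version ranged from 0.858 - 0.863 = -0.005 to 0.861 - 0.706 = +0.155, or about 0 to +16 points. Completers only ranged from 0.579 - 0.757 = -0.178 to 0.829 - 0.706 = +0.123.

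Two limits apply. No simulated scenario had gait speed predicting better than TUG; step 3 covers that case. The indicator column replaces gait speed rather than adding to it. One shorter run (250 replicates, correlations 0.7 and 0.7, 10% unable) fitted both and gave power 0.90, against 0.87 for gait speed alone.

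**The case against.** Gait speed is a coherent choice for this population. The trial enrols non-ambulant people and stratifies on mobility level. Gait speed has a value for all of them, because inability scores 0 m/sec, whereas the article defines no TUG value for someone who cannot do the test. Adjusting for baseline TUG as recorded would drop these people and could cost more power than it gains, as the completers-only column shows. The plan does not leave baseline mobility out; it adjusts for a closely related test. Baseline TUG is also used elsewhere, in the exploratory longitudinal analysis of all outcomes. TUG at discharge is one of several secondary outcomes that the article describes as supplementing the primary analysis.

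All of that stands, and it rules out a plain swap. It does not answer the case for adding baseline TUG beside gait speed with a code for inability, which keeps every participant and parallels the article's own scoring of gait speed. The objection that the gain is unproven also stands and limits how the point may be put.

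**Conclusion.** The inconsistency is a fact of the text. The cost is probable but unquantified: some precision is likely left unused in one supplementary secondary comparison. The range of about 0 to +16 points of power rests on assumed correlations, an assumed 0.4 SD effect and assumed shares unable at baseline, none of which the article gives for TUG.

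A reader might infer three stronger things that the document does not support:

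- **That precision is certainly lost.** This requires baseline TUG to predict discharge TUG beyond gait speed, and no correlation is reported. In step 3, gait speed at 0.7 with TUG at 0.6 yields a ratio of only 1.01.
- **That the hazard ratio is biased toward 1.** Attenuation depends on the prognostic information remaining after gait speed, which is unknown. A hazard ratio conditional on a different covariate set is a different quantity, not a biased one. No type I error problem arises.
- **That the gain equals a fixed share of extra participants.** Putting an R^2 of 0.10 or 0.20 into 1/(1 - R^2) gives 1.11 or 1.25, but those R^2 values are assumed, exclude a nil gain, and enter a linear-model formula.

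This is a minor improvement. The primary analysis, the 69 per group and the total of 198 do not change.

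**What to change.** In the discharge TUG Cox model, keep baseline gait speed and add baseline TUG in a form defined for everyone: either 1/TUG with 0 for those unable, or TUG plus an indicator for inability. Include site and mobility level, since randomization is stratified on both. State how people unable to do the TUG at discharge enter the model. Do not simply replace gait speed by baseline TUG in completers.

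The cost is a short change of wording and three or four degrees of freedom: one or two for TUG, one for the two sites and one for the two mobility levels. Under the settings used above, about 148 x 0.86 = 127 participants would have a timed discharge TUG, so this is affordable. The two baseline mobility measures will be collinear, and an indicator for inability will overlap with the non-ambulant stratum. This does not harm the treatment comparison, but the individual covariate coefficients should not be interpreted. If the sponsor prefers gait speed alone, a sentence giving the reason, with the extended model as a sensitivity analysis, would be enough.
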